### 8.2.5 Day 15 ( $\pm 2$ Days)

The following assessments are to be carried out on Day 15 ( $\pm 2$  days) (NB day of randomisation and start date of treatment is Day 1). This differs from the Master protocol as +1 day is permitted to this visit date.

- SARS-CoV-2 surveillance NP swab
- Assessment using the WHO Clinical Progression Scale (WHO, 2020):
  0. Uninfected, no viral RNA detected
  1. Ambulatory mild disease, asymptomatic; viral RNA detected
  2. Ambulatory mild disease, symptomatic; independent
  3. Ambulatory mild disease, symptomatic; assistance needed
  4. Hospitalised moderate disease, no oxygen therapy (If hospitalised for isolation only, record stats as for ambulatory patient)
  5. Hospitalised moderate disease, oxygen by mask or nasal prongs
  6. Hospitalised severe disease, oxygen by NIV or high flow
  7. Hospitalised severe disease, intubation and mechanical ventilation  $pO_2/FiO_2 \geq 150$  or  $SpO_2/FiO_2 \geq 200$
  8. Hospitalised severe disease, mechanical ventilation  $pO_2/FiO_2 < 150$  ( $SpO_2/FiO_2 < 200$ ) or vasopressors
  9. Hospitalised severe disease, mechanical ventilation  $pO_2/FiO_2 < 150$  and vasopressors, dialysis, or ECMO
  10. Dead
- Non-Ventilated Patients: National Early Warning Score 2 (NEWS2) Assessment:
  - Respiration rate
  - Oxygen saturation
  - Systolic blood pressure
  - Pulse rate
  - Level of consciousness or new confusion\*
  - Temperature

\*The patient has new-onset confusion, disorientation and/or agitation, where previously their mental state was normal – this may be subtle. The patient may respond to questions coherently, but there is some confusion, disorientation and/or agitation. This would score 3 or 4 on the GCS (rather than the normal 5 for verbal response), and scores 3 on the NEWS system.
- Full blood count
- Urea and electrolytes
- Estimated GFR
- Liver Function Tests
- Uric acid
- Concomitant medication and standard of care review
- AE assessment
- Assessment of oxygen use (low flow, high flow, mechanical flow, mechanical ventilation use) (only if supplemental oxygen is not administered) – daily whilst in hospital
  - Chest X-Ray (if clinically indicated)

In addition, for candidate specific trial protocol the following are required:

- Targeted physical exam
- Blood collection for translational research

### **Day 29 ( $\pm 2$ days)**

The following assessments are to be carried out on Day 29 (+2 days) (NB day of randomisation and start date of treatment is Day 1).

- SARS-CoV-2 surveillance NP swab
- Assessment using the WHO Clinical Progression Scale (WHO, 2020):
  0. Uninfected, no viral RNA detected
  1. Ambulatory mild disease, asymptomatic; viral RNA detected
  2. Ambulatory mild disease, symptomatic; independent
  3. Ambulatory mild disease, symptomatic; assistance needed
  4. Hospitalised moderate disease, no oxygen therapy (If hospitalised for isolation only, record stats as for ambulatory patient)
  5. Hospitalised moderate disease, oxygen by mask or nasal prongs
  6. Hospitalised severe disease, oxygen by NIV or high flow
  7. Hospitalised severe disease, intubation and mechanical ventilation  $pO_2/FiO_2 \geq 150$  or  $SpO_2/FiO_2 \geq 200$
  8. Hospitalised severe disease, mechanical ventilation  $pO_2/FiO_2 < 150$  ( $SpO_2/FiO_2 < 200$ ) or vasopressors
  9. Hospitalised severe disease, mechanical ventilation  $pO_2/FiO_2 < 150$  and vasopressors, dialysis, or ECMO
  10. Dead
- Non-Ventilated Patients: National Early Warning Score 2 (NEWS2) Assessment:
  - Respiration rate
  - Oxygen saturation
  - Systolic blood pressure
  - Pulse rate
  - Level of consciousness or new confusion\*
  - Temperature

\*The patient has new-onset confusion, disorientation and/or agitation, where previously their mental state was normal – this may be subtle. The patient may respond to questions coherently, but there is some confusion, disorientation and/or agitation. This would score 3 or 4 on the GCS (rather than the normal 5 for verbal response), and scores 3 on the NEWS system.
- Full blood count
- Urea and electrolytes
- Estimated GFR
- Liver Function Tests
- Uric acid
- Concomitant medication and standard of care review
- AE assessment
- Targeted physical exam
- Urine pregnancy test for WOCBP
- Urinalysis

## **8.3 SAMPLE REQUIREMENTS**

**This section differs from the Master Protocol and is specific to this candidate.**

Samples will be collected in accordance with the laboratory manual and schedule of observations and procedures (Section 8.2). Sponsor may store samples for up to 25 years after the end of the study to achieve study objectives.

## Pharmacodynamics

### 8.3.1 Viral Swabs

Patients will be asked to give consent for use of their PCR nasal swabs collected at every clinic visit including baseline and all treatment and follow-up visits. This is mandatory for phase I and II.

The same samples used for SARS-CoV-2 PCR will be used, so collection and labs will be as standard clinical practice.

Patients will have the option to consent for an additional PCR nasal swab to be collected on days 1, 3 and 5 for use in future translational research.

### 8.3.2 Pharmacokinetics

#### Phase I

All patients will be asked to give consent for collection of blood, tears, saliva, and nasal secretions for paired measurement of drug concentrations. Samples will be collected after first dose, on Day 1, Day 3 and Day 5 of treatment according to the timing windows below, recognising that a pragmatic, opportunistic sampling approach is required to sample patients receiving non-invasive ventilatory support (NIV) during periods when NIV is paused as part of clinical care.

| Matrix                        | Sample Type/Collection Tube   | Day 1 & Day 3  |                                       |                |                | Day 5          |                |
|-------------------------------|-------------------------------|----------------|---------------------------------------|----------------|----------------|----------------|----------------|
|                               |                               | pre-dose       | Time post-completion of infusion (hr) |                |                | 0-1 hr         | 6-12 hr        |
|                               |                               |                | 0-1 hr                                | 2-4 hr         | 6-12 hr        |                |                |
| Plasma            | K2 EDTA tube (2 mL)           | X              | X                                     | X              | X              | X              | X              |
| Dried Blood Spot  | Hemasep card (2 x spots)      | X a | X a                        | X a | X a | X a | X a |
| Tears             | 2 x Schirmer Tear Test Strips |                |                                       |                | X              |                |                |
| Saliva            | Salivette tube                |                |                                       |                | X              |                |                |
| Nasal secretions  | 2 x nasal swabs (SAM)         |                |                                       |                | X              |                |                |
| PBMC              | 1 x CPT (8 mL)                |                |                                       |                | X              |                | X              |

 For patients who are on NIV, sampling is pragmatic and opportunistic, and may be omitted according to physician discretion

a 2 x 100 µL whole blood taken from K2 EDTA tube, prior to centrifugation, and spot onto DBS card

| PK Sample Kit |
|---------------|
| PK 1          |
| PK 2          |
| PK 3          |

**PK Sample Kit 1 (PK1):** for collection and processing of whole blood [plasma + DBS] on Day 1 & Day 3 [pre-dose, 0-1 hr, 2-4 hr] and Day 5 [0.1 hr]

**PK Sample Kit 2 (PK2):** for collection and processing of PBMC and all plasma and non-plasma samples on Day 1 & Day 3 [6-12 hr timepoint]

**PK Sample Kit 3 (PK3)** = for collection and processing of plasma + DBS and PBMC on Day 5 [6-12 hr timepoint]

## Phase II

For phase II, patients may choose to give optional consent for the PK sub study. Sparse sampling (plasma only; maximum of 4 time points per patient) will be undertaken over the duration of treatment, with opportunistic sampling timed to coincide with any pause in delivery of NIV that is scheduled as part of clinical care.

All samples will need to be processed and frozen for batch shipment to Bioanalytical Facility, University of Liverpool.

Further details are provided in the lab manual.

### ***Safety Laboratory Evaluations***

This information is in addition to the Master Protocol.

Blood samples will be collected for safety laboratory evaluations at the timepoints indicated above. Additional clinical laboratory evaluations will be performed at other times if judged to be clinically appropriate, required by hospital policy (e.g. MRSA and SARS-CoV-2 screening) or if the on-going review of the data suggests a more detailed assessment of safety laboratory evaluations is required. An investigator will perform a clinical assessment of all clinical laboratory data. Samples will need to be processed at site and will be analysed by the local site laboratory.

## **8.4 DEVIATIONS AND SERIOUS BREACHES**

Refer to the AGILE Master Protocol section 8.4, with addition of CRO to be informed of all deviations and serious breaches. Candidate specific information relating to serious breaches reporting is listed in section 8.4 which supersedes information in the corresponding section of the AGILE Master Protocol.

Additionally, the site and Sponsor will adopt all reasonable measures to record data in accordance with the protocol. It is accepted, however, that some minor variations may occur in the day to day conduct of the study. All such deviations will be documented in the Investigator Site File and Trial Master File (recorded by CRO), with the reasons for their occurrence. Where appropriate, the deviations will be detailed in the clinical study report.

All serious breaches of Good Clinical Practice and/or the trial protocol will be reported to the regulatory authorities and other organisations, as required in the Medicines for Human Use (Clinical Trials) Regulations 2004, as amended but no later than 7 days of the Sponsor/CRO becoming aware

CST-6 reporting responsibilities as per CST-6 Trial Matrix Allocation (TAM).

## 9 SAFETY

### 9.1 SAFETY EVENT REPORTING:

Refer to the AGILE Master protocol for definitions. As per the Master the below information has been added specific to the candidates under investigation in this protocol.

#### 9.1.1 Dose Limiting Toxicity (DLT)

Dose limiting toxicities will be defined as CTCAE v5 Grade  $\geq 3$  adverse events, independently assessed to be possibly or probably related to the IMP as per SRC charter. The assessment of relatedness is included in the DLT definition for this CST due to the potential for a high frequency of CTCAE v5 Grade  $\geq 3$  adverse events related to disease or co-morbidity in these cohort of hospitalised patients and the desire to avoid labelling potential treatments as unsafe due to misclassifying non-treatment related toxicities.

### 9.2 REPORTING WINDOWS

All AEs will be collected up to Day 29 post-dose. SAEs will be collected from dose administration through to Day 29 follow-up visit. However, any SAEs assessed as related to study participation (e.g., study intervention, protocol-mandated procedure, invasive tests or change in existing therapy) will be recorded from the time participant consents to participate in the study.

Each time there is a change in grade of an adverse event this should be recorded on a separate log line on the adverse event form on the eCRF. Refer to the eCRF Guidance on how to report this on Rave. The investigator should notify the trial sponsor of any death or adverse event occurring at any time after a patient has discontinued or terminated trial participation that may reasonably be related to this trial.

### 9.3 ADVERSE EVENT TERM AND SEVERITY GRADE

Refer to the AGILE Master Protocol section 9.3

### 9.4 SERIOUSNESS

Refer to the AGILE Master Protocol section 9.4

Additionally, all SAEs must be reported immediately by the PI or delegate at the participating centre to the CRO using study specific SAE form.

#### 9.4.1 Exceptions

**Note that this section differs from the AGILE Master Protocol**

For the purposes of this trial, the following SAEs do not require reporting to SCTU using the Serious Adverse Event Report Form:

- Death due to disease progression of COVID-19 – This is the condition for which the participant is being treated. Unless death is considered related to the candidate.
- Any other as appropriate e.g. SAEs occurring prior to trial treatment/intervention, that are not considered to be related to trial procedures
- SAEs occurring prior to the first dose of the candidate, that are not considered to be related to trial procedures

### 9.5 CAUSALITY

Refer to the AGILE Master Protocol section 9.5

## 9.6 EXPECTEDNESS ASSESSMENT:

There are no expected events associated with Favipiravir, hence all SARs are to be considered SUSARs.

Refer to the Investigator's Brochure for the current Reference Safety Information including ADRs and to the AGILE Master protocol for additional safety considerations.

| Name of Product     | IB | Section/Table No. | Manufacturer                      | Date of text revision DD-MMM-YYYY |
|---------------------|----|-------------------|-----------------------------------|-----------------------------------|
| T-705 (Favipiravir) | 3  | Section 6         | Fujifilm Toyama Chemical Co., Ltd | 02-FEB-2022                       |

## 9.7 REPORTING PROCEDURES

Refer to the AGILE Master Protocol section 9.7 for full details of reporting procedures. Candidate specific information relating to pregnancy reporting is listed in section 9.7.1 which supersedes information in the corresponding section of the AGILE Master Protocol.

### 9.7.1 Pregnancy

- Details of all pregnancies in female participants will be collected after the start of study intervention and until Week 24 via telephone consultation.
- If a pregnancy is reported, the investigator will record pregnancy information on the appropriate form and submit it to sponsor or designee within 24 hours of learning of the female participant pregnancy. While pregnancy itself is not considered to be an AE or SAE, any pregnancy complication or elective termination of a pregnancy for medical reasons will be reported as an AE or SAE.
- Abnormal pregnancy outcomes (e.g., spontaneous abortion, fetal death, stillbirth, congenital anomalies, ectopic pregnancy) are considered SAEs and will be reported as such.
- The participant will be followed to determine the outcome of the pregnancy. The investigator will collect follow-up information on the participant and the neonate and the information will be forwarded to the sponsor or designee.
- Any post-study pregnancy-related SAE considered reasonably related to the study intervention by the investigator will be reported to the sponsor or designee. While the investigator is not obligated to actively seek this information in former study participants, he or she may learn of an SAE through spontaneous reporting.
- Any female participant who becomes pregnant while participating in the study will be withdrawn from the study.

## 9.8 CLINICAL RESEARCH ORGANISATION (CRO) RESPONSIBILITIES FOR SAFETY REPORTING TO REC

PHARMExcel (CRO) will have expedited reporting responsibilities to REC as the CRO for this trial.

Urgent Safety Measure (USM) reporting will be undertaken by SCTU.

DSUR preparation will be undertaken as per the CST-6 TAM and reporting undertaken by SCTU.

## 9.9 CLINICAL RESEARCH ORGANISATION (CRO) RESPONSIBILITIES FOR SAFETY REPORTING TO MHRA

PHARMExcel (CRO) will have expedited reporting responsibilities to MHRA as the CRO for this trial.

Urgent Safety Measure (USM) reporting will be undertaken by SCTU.

DSUR preparation will be undertaken as per the CST 6 TAM and reporting undertaken by SCTU.

## **9.10 EMERGENCY UNBLINDING (PHASE II ONLY)**

**This section is in addition to the Master Protocol.**

Patient allocation will be provided to unblinded pharmacy staff via an IWRS. The randomisation code will be retained by the system.

Deaths and serious adverse events (SAE) will be reviewed in a blinded manner. If a cause of death or SAE is unexpected (i.e. not listed in the RSI approved section of the IB) and considered drug related the trial statistician and Quality and Regulatory team (SCTU) will be able to unblind the patient's treatment assignment.

24hr emergency unblinding service will be provided through the IWRS system. Sites must have tested procedure for out-of-hours emergency unblinding.

In the case of adverse events in which patient care would vary dependent on treatment allocation, emergency unblinding may be performed by unblinded pharmacy staff or in cases where it is the site's local policy for on-call doctors to unblind, this will be permitted. In these situations, discussion with the Chief Investigator is not required. If patient allocation is disclosed, sites should report to SCTU the date, time, reason for unblinding, name of person requesting the code break, and name of person breaking the code using the trial specific Emergency Unblinding Notification Form. Unblinding reports should be filed in the patient's medical records at site and in the trial master file (without disclosing the treatment allocation).

The Trial Manager or Senior Trial Manager will ensure that the Statistician and Senior Statistician are fully informed of all cases of unblinding. A participant may continue in the study if that participant's intervention assignment is unblinded, providing there are no safety issues. Potential continuation should be the decision of the treating physician.

All further details are outlined in the study specific procedure for unblinding.

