### 1.3 SCHEDULE OF OBSERVATIONS AND PROCEDURES (Phase I and II)

|                                                       | Screening k | Day 1
(baseline) | Daily
whilst in hospital
(days 2-14) | Specific Assessments on
Days 3, 5, 8, 11 (±1 days) | Day 15
(±2 days) | Day 29
(±2 days) |
|-------------------------------------------------------|------------------------|---------------------|--------------------------------------------|-------------------------------------------------------|---------------------|---------------------|
| Informed consent                                      | X                      |                     |                                            |                                                       |                     |                     |
| Check Eligibility                                     | X a         | X                   |                                            |                                                       |                     |                     |
| Randomisation                                         |                        | X                   |                                            |                                                       |                     |                     |
| Telephone Contact b (AEs, Con-Meds)        |                        |                     | Daily apart from in hospital               |                                                       |                     |                     |
| Demographics                                          | X                      |                     |                                            |                                                       |                     |                     |
| Treatment compliance - up to day 7                    |                        |                     | X (Day 2 to 7)                             |                                                       |                     |                     |
| AE/SAE assessment                                     | X (from consent)       | X                   | X                                          | X                                                     | X                   | X                   |

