## 8.2 TRIAL PROCEDURES

Participants will receive treatment up to 7 days when hospitalised for COVID-19 and cease when they have been discharged from hospital. Visits outlined in the schedule of events will take place as in-patients when in hospital or out-patient. If discharged participants are not able to return after discharge for clinic visits, follow-up should be done by phone call to the patient and a

minimised criteria will apply to perform AE assessment, concomitant medication and patient status.

**Note that this CST visit schedule differs from the Master Protocol and is the schedule to be used for all patients enrolled onto this candidate specific trial.**

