## **Analysis**

Patients will be analysed according to the treatment to which they were randomised (efficacy population). In addition, a supplementary analysis of the primary endpoint will be conducted in all patients for whom there were no major protocol deviations that could impact treatment efficacy (to be defined in the statistical analysis plan).

The primary efficacy endpoint in phase II of the SARS-CoV-2 viral load (in log10) will be analysed using a Bayesian repeated measures model including all post-randomisation assessments up to and including Day 3. The model will adjust for treatment, baseline viral load, visit timepoint and interaction of treatment by visit, with a subject-specific random-effect and unstructured variance-covariance matrix. A non-informative (vague) prior will be used for all model parameters. Viral load data will be log10-transformed prior to analysis with treatment differences expressed on the log10 scale. If 94% of the posterior distribution of the treatment effect is below 0 (i.e. in favour of Favipiravir), the study will conclude the treatment is efficacious, at the interim or the final analysis.

For any deaths in the trial, the change in viral load will be assumed to be zero from the last measured timepoint. To assess the impact of missingness in the primary analysis due to missing data that are not missing at random (including death) sensitivity analyses will be performed. Details will be provided in the statistical analysis plan.

Once the last participant recruited completes the Day 29 assessment the data will be unblinded to allow a primary readout of this endpoint. Participants will continue to complete the remaining scheduled assessments and will not be unblinded at an individual level.

Further details on analysis methods for other endpoints will be detailed in a detailed SAP, which will be finalised and signed off prior to database lock.

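### Section 9.10 ties an unblinded participant's continuation in the study to the absence of safety issues; the condition should govern study treatment only, so that follow-up to Day 29 is kept (minor wording correction)

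*Protocol*

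**What the plan says.** Protocol section 9.10 (Emergency unblinding, phase II only) contains the rule. It begins "A participant may continue in the study if that" and, after one linking word, goes on "intervention assignment is unblinded, providing there are no safety issues. Potential continuation should be the decision of the treating physician".

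The same section gives two routes to unblinding:

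- The trial statistician and the quality and regulatory team can unblind a death or SAE that is unexpected and considered drug related.
- Site pharmacy staff, or on-call doctors where local policy allows, can unblind. The trigger is "In the case of adverse events in which patient care would vary dependent on treatment allocation". The Chief Investigator need not be consulted.

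Elsewhere the protocol treats dosing and participation separately. Section 8.2 says "Participants will receive treatment up to 7 days when hospitalised for COVID-19 and cease when they have been discharged from hospital", and then "Visits outlined in the schedule of events will take place as in-patients when in hospital or out-patient". A discharged participant who cannot return is followed by phone, where "minimised criteria will apply to perform AE assessment, concomitant medication and patient status". The schedule in section 1.3 has a row "Treatment compliance - up to day 7", while its visits run to Day 29. Section 6.7 describes stopping for safety as stopping study treatment and points to section 7. The title of section 7 names the two kinds of stopping separately, and its content is deferred to Master Protocol section 7.0.

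**The concern.** A participant is unblinded because something has gone wrong clinically. A rule that then allows continued participation only where there are no safety issues could remove from follow-up the participants whose later course matters most for the safety profile. After site unblinding, the physician who decides may also know the arm, so the loss could differ between favipiravir and placebo.

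The outcomes exposed are those after dosing: mortality, discharge, WHO scale, new mechanical ventilation, AEs and SAEs, and viral load out to Day 29. Section 10.3.2 counts everyone randomised in the efficacy population. A participant whose follow-up ended this way would therefore still be counted, but with these outcomes missing for a reason related to toxicity. The analysis can model missing data, but it cannot recover follow-up that a site was allowed to end.

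**Working it through.** The main question is what the rule attaches to, so most of the check is a comparison of the protocol's own provisions. The sample-size figure is then reproduced to confirm that the design is not at stake.

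**1. What the condition governs.**

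| Section | Event | What stops |
|---|---|---|
| 6.7 | Safety reason | Study treatment |
| 8.2 | Discharge | Treatment; visits continue, by phone if necessary |
| 9.7.1 | Pregnancy | Participation, by explicit instruction to withdraw |
| 9.10 | Unblinding with a safety issue | Permission to continue in the study |

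The protocol has separate terms for treatment and participation. Section 9.10 uses the participation term in a setting where the decision normally needed is about dosing.

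**2. When it applies.** The site route requires an adverse event whose care depends on allocation. The central route requires a death or an unexpected, drug-related SAE. Section 9.6 lists no expected events, so any serious adverse reaction can open the central route. A safety question is therefore already open when the continuation rule is read. The point that the physician may know the arm applies to the site route; 9.10 does not say that central unblinding is passed on to the treating physician.

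**3. What lies beyond dosing.** Treatment lasts up to Day 7. The fixed mortality time points in section 3.2 are Days 8, 15 and 29, so 3 of 3 fall after Day 7. So do the fixed time points for discharge and WHO-scale improvement (also Days 8, 15 and 29) and the later swabs.

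**4. What would still be captured.** Section 9.2 collects AEs and SAEs to Day 29. Once participation has ended, it asks only for deaths or events that may reasonably be related to the trial. Section 9.4.1 exempts deaths from COVID-19 progression from the SAE form unless they are considered related. An unrelated COVID-19 death after removal would belong in the mortality endpoint, but this document shows no route that would capture it.

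**5. The primary endpoint and power.** Inputs from sections 10.2 and 10.3.2: 33 per arm at the interim, 99 per arm at the end, SD 1.5, efficacy if the posterior probability exceeds 0.94 (interim or final), futility if it is below 0.30 at the interim. With a vague prior the posterior probability is approximately Φ(Z), so the bounds are z(0.94) = 1.555 and z(0.30) = −0.524. Information is I = n/(2 × 1.5²) = n/4.5, the mean of Z is δ√I, and the correlation between the two looks is √(33/99) = √(1/3).

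At δ = 0.5, the interim mean is 0.5 × √(33/4.5) = 1.354, and the chance of stopping for efficacy is Φ(1.354 − 1.555) = 0.420. The final-stage term comes from bivariate normal integration.

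| True effect (log10) | Interim success | Final success | Total | Plan states |
|---|---|---|---|---|
| 0 | 0.0600 | 0.0398 | 0.0998 | below 10% |
| 0.5 | 0.4204 | 0.3837 | 0.8042 (rounded) | 80% |
| 0.6 | 0.5279 | 0.3758 | 0.9037 | over 90% |

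A simulation with 2 million replicates gave 0.0999, 0.8044 and 0.9036. The plan's figures reproduce, and a wording change leaves them as they are.

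The documents give no unblinding rate. Purely as an assumed range, suppose a share of participants had no primary data at all. Power at 0.5 log10 would then be 0.801 (1%), 0.798 (2%), 0.788 (5%) or 0.771 (10%), with type I error 0.0998 throughout. This overstates any effect of 9.10, because only someone unblinded and taken out of follow-up before the Day 3 swab would lose the primary outcome. These figures are a ceiling for the primary endpoint and do not measure the harm.

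**The case against.** The strongest reply is that no loss has been shown. Section 9.10 is written as an addition to the Master Protocol and refers to a study-specific unblinding procedure for further detail. Rules on follow-up after stopping treatment belong in Master Protocol section 7.0. Neither document is shown, and either may require follow-up to Day 29. This stands as a limit on what can be claimed. It does not correct 9.10, because a site that reads 9.10 finds a trial-specific sentence that conditions participation on safety.

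The second reply is that the sentence is permissive. A reader might infer that an unblinded participant with a safety issue must be withdrawn. The text does not say so, and 9.7.1 shows that the protocol states mandatory withdrawal plainly when it means it. The wording permits follow-up to end; it does not require it. Leaving the choice to the treating physician is also what one would expect if the authors had dosing in mind, and safety issues could be read narrowly as problems with further exposure. That may be the intention, but the sentence does not say it.

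A reader might also infer a contradiction with the intention-to-treat analysis. There is none. That population is defined by randomisation, and missing outcomes do not alter who belongs to it. The issue is incomplete data within the population.

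**Conclusion.** The point holds as a minor wording correction. Section 9.10 attaches a safety condition to study participation where it should attach to study treatment. Because safety events trigger unblinding, the wording permits follow-up to end for reasons linked to toxicity and possibly to arm. Safety, mortality and clinical outcomes from Day 8 to Day 29 are exposed in what is probably a handful of participants. The size is unknown because no unblinding rate is given.

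A stronger reading, that the primary analysis or its power is compromised, is not supported. The endpoint is at Day 3, and the stated operating characteristics reproduce and do not change with the fix. Nor can it be said that the trial as a whole lacks a rule keeping follow-up, since the Master Protocol and the unblinding procedure are not available. The conclusion rests on the words of 9.10 and on how the rest of this protocol separates treatment from participation.

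**What to change.** Replace the continuation sentences in 9.10 with:

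> After unblinding, the treating physician decides whether study treatment continues; it stops if there are safety issues. Unblinding or stopping treatment does not end study participation: scheduled assessments continue to Day 29 (by phone as in 8.2 if the participant cannot attend) unless consent to follow-up is withdrawn or section 9.7.1 applies.

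The reference to 9.7.1 is needed because that section requires withdrawal on pregnancy; leave 9.7.1 itself unchanged. The phone fallback covers adverse events, concomitant medication and patient status but not swabs, so some late viral load data may still be missing.

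The cost is a short text change, matched in the unblinding procedure and checked against Master Protocol section 7.0. It adds no patients, visits or procedures, and the sample size, power and type I error stay as stated.
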